# Study protocol: a multicentre, open-label, parallel-group, phase 2, randomised controlled trial of autologous macrophage therapy for liver cirrhosis (MATCH)

**DOI:** 10.1136/bmjopen-2021-053190

**Published:** 2021-11-08

**Keywords:** hepatobiliary disease, immunology, clinical trials, cell biology

## Abstract

**Introduction:**

Liver cirrhosis is a growing global healthcare challenge. Cirrhosis is characterised by severe liver fibrosis, organ dysfunction and complications related to portal hypertension. There are no licensed antifibrotic or proregenerative medicines and liver transplantation is a scarce resource. Hepatic macrophages can promote both liver fibrogenesis and fibrosis regression. The safety and feasibility of peripheral infusion of ex vivo matured autologous monocyte-derived macrophages in patients with compensated cirrhosis has been demonstrated.

**Methods and analysis:**

The efficacy of autologous macrophage therapy, compared with standard medical care, will be investigated in a cohort of adult patients with compensated cirrhosis in a multicentre, open-label, parallel-group, phase 2, randomised controlled trial. The primary outcome is the change in Model for End-Stage Liver Disease score at 90 days. The trial will provide the first high-quality examination of the efficacy of autologous macrophage therapy in improving liver function, non-invasive fibrosis markers and other clinical outcomes in patients with compensated cirrhosis.

**Ethics and dissemination:**

The trial will be conducted according to the ethical principles of the Declaration of Helsinki 2013 and has been approved by Scotland A Research Ethics Committee (reference 15/SS/0121), National Health Service Lothian Research and Development department and the Medicine and Health Care Regulatory Agency-UK. Final results will be presented in peer-reviewed journals and at relevant conferences.

**Trial registration numbers:**

ISRCTN10368050 and EudraCT; reference 2015-000963-15

Strengths and limitations of this studyFirst randomised controlled trial of an innovative cell-based therapy for cirrhosis.Range of evidence-based non-invasive assessments of liver fibrosis and function.Concurrent longitudinal measurement of health-related quality of life in an important chronic liver disease population.Open-label design, but outcome assessors blinded to treatment allocation.

## Introduction

Liver disease is responsible for almost 2 million deaths per year globally, 1 million directly relating to complications of end-stage liver failure and a further 1 million due complications of hepatitis including hepatocellular carcinoma (HCC).^1^ Cirrhosis and liver cancer are now, respectively, the 11th and 16th most common cause of death globally, accounting for 3.5% of all deaths. Variation in liver disease epidemiology occurs relative to the prevalence of modifiable risk factors including harmful alcohol ingestion, obesity/metabolic syndrome and viral hepatitis.^2^ Worldwide there were 10·6 million prevalent cases of decompensated cirrhosis and 112 million prevalent cases of compensated cirrhosis in 2017.^3^

Cirrhosis represents the end-stage of chronic liver injury and progressive fibrosis (scarring), irrespective of the underlying aetiology. It is characterised by severe liver fibrosis leading to architectural disruption, hepatocyte dysfunction and portal hypertension. Cirrhosis typically affects those of working age, which has broad socioeconomic impacts. Furthermore, cirrhosis impairs health-related quality of life (HRQoL) including mental health and physical factors and reduced ability to perform activities of daily living^4^; those with primary biliary cholangitis (PBC), non-alcoholic fatty liver disease (NAFLD) and hepatitis C virus (HCV) appear disproportionately affected.^5^

The classical dichotomy of chronic liver disease staging is compensated (asymptomatic) or decompensated cirrhosis. Acute decompensation delineates the development of one or more associated sequelae and is a key prognostic inflection point. The transition from compensated to decompensated cirrhosis occurs at a rate of about 5%–7% per year.^6^ Decompensation represents a prognostic milestone as it significantly alters mortality, with a cumulative 1-year mortality of 77% for those with stage 3 and 4 decompensated disease vs 4.4% in those with compensated disease. Importantly, emergency hospitalisation for decompensated liver disease heralds a deterioration in a patient’s prognosis independent of stage of cirrhosis.^7^

Cirrhosis decompensation heralds the development of widespread organ dysregulation, including portal hypertension, splanchnic vasodilation, left ventricular impairment and systemic immune dysfunction. Inflammatory mediators of liver disease may underpin and potentiate nitric oxide-mediated capillary dysfunction, direct immunocytopathy and induce significant metabolic derangement and redistribution of essential nutrient precursors.^8^

For patients in whom disease-specific therapy is unsuccessful or not possible, treatment options remain limited. Presently, although numerous agents have been evaluated in clinical trials, there are no approved pharmacological therapies for reversing fibrosis or stimulating liver regeneration in the cirrhotic liver.^9^ Liver transplantation remains the only curative option for those with end-stage cirrhosis or HCC. Unfortunately, a significant proportion of those referred for transplant assessment are ineligible and ~12% die annually while on the waiting list in the UK.^10 11^ Those who do undergo liver transplantation require lifelong immunosuppression with inherent risks of toxicity and adverse effects.^12^

Although whole organ or split liver transplantation are well established procedures to reinstate liver functional capacity, cell-based transplantation approaches are emerging.^13^ Successful cell therapy could theoretically overcome organ availability limitations, while avoiding invasive surgical interventions. Successful hepatocyte transplantation involves reconstitution of as little as 1%–2.5% of functional tissue across a range of inherited metabolic liver diseases and highlights the utility of such approaches.^14^ Furthermore, there is a requirement for treatments that can ‘bridge’ patients with cirrhosis until a donor organ is available or allow spontaneous regeneration to occur following acute liver failure. Cell therapies that sufficiently modulate cirrhosis by reducing fibrosis and stimulating liver function may also promote endogenous tissue repair and regeneration such that the need for transplantation is delayed or obviated.

Previous studies have typically focused on the use of mesenchymal stem cells (MSCs), hepatocyte stem cells and heterogeneous cell populations which will include proinflammatory and profibrotic cell lineages. Despite promising preclinical studies, randomised controlled trials (RCTs) of autologous cell therapies in cirrhosis have so far been disappointing.^15 16^

Macrophages are a heterogeneous, highly plastic population of cells with a diverse spectrum of roles within the liver including phagocytosis and maintenance of immune tolerance. Hepatic monocyte-derived macrophages are known to play a dual role in liver fibrosis. During chronic liver injury models they mediate the recruitment of proinflammatory cells and activation of hepatic stellate cells to promote fibrogenesis.^14^ Conversely, fibrosis regression is characterised by an in situ phenotypic switch to a restorative hepatic macrophage population with pro-resolution properties^17^ whereby liver repair and regeneration is facilitated by increased expression of matrix metalloproteinases (MMPs), growth factors and phagocytosis-related genes.^18 19^ This process of phenotypic ‘switching’ from a proinflammatory ‘M1-like’ moiety, to a pro-resolution ‘M2-like’ macrophage is mediated via down-regulation of NOD-containing, LRR-containing and pyrin domain-containing protein 3.^14^

In a mouse model of chronic liver injury, cell therapy with unmanipulated syngenic macrophages reduced fibrosis and improved markers of liver function.^20^ Furthermore, infusion of human macrophages (differentiated from cirrhotic patients’ apheresis-derived CD14^+^ monocytes) also resolved liver fibrosis in mice, indicating their suitability for clinical therapy.^18 20 21^

We recently demonstrated the feasibility of performing apheresis in cirrhotic patients and differentiating autologous bone marrow derived monocytes into macrophages.^22^ This process includes specific CD14^+^ monocyte isolation from peripheral circulation leucopharesis collections using CliniMACS automated separation device, a closed system, where the product is incubated with CD14 labelled magnetic beads, allowing separation of CD14^+^ cells when passed over a magnetic column. Selected CD14^+^ monocytes are counted and resuspended in differentiation medium containing 100 ng/mL macrophage colony-stimulating factor (M-CSF). Cells are placed into closed system, low adhesion culture bags at optimum cell density (2×10^6^ cells per mL and per cm^3^). Cells are cultured in a humidified atmosphere at 37°C, with 5% CO2, for 7 days. Media replenishment is undertaken twice during culture (typically days 3 and 5), using differentiation media supplemented with 100 ng/mL M-CSF. Flow cytometry is used to determine cell viability and phenotype cell populations premonocyte and postmonocyte selection and postmacrophage differentiation prior to product release, this has been validated for 7-day and 10-day time points.

We also have extensive preclinical data demonstrating that peripherally injected macrophages hone to the liver (predominantly) and spleen (after passing rapidly through the lungs) and that this process in enhanced in the presence of liver damage.^20 23^ Furthermore, in a first-in-human study we confirmed the safety, feasibility and maximum achievable dose of autologous macrophages.^24^ The study was not controlled, and therefore, unable to evaluate efficacy. However, we observed some initial signals related to enhanced fibrosis remodelling and liver function that warranted assessment in an RCT as presented here.

### Objectives

The primary objective of this phase 2 RCT is to evaluate whether there is an improvement in liver function at 3 months in patients receiving autologous macrophage therapy compared with standard medical care.

The secondary objectives are to assess any improvement in markers of liver fibrosis, increased disease related quality of life, reduced liver related clinical events and prolonged transplant-free survival.

### Trial design

The MATCH trial is designed as a multicentre, open-label, parallel-group, phase 2, RCT to compare autologous macrophage therapy with standard medical care in patients with compensated cirrhosis. Randomisation will be performed with a 1:1 allocation ratio and the primary outcome is the baseline to 90-day change in Model for End-Stage Liver Disease (MELD) score. Figure 1 provides an overview of trial pathway following randomisation to the respective arms. Initially, the proposed trial was designed to administer three infusions to those randomised to the treatment arm. It became apparent that it would not be acceptable or feasible to continue with three infusions due to the onerous commitment required of participants and the challenge to complete the trial within the proposed time frame. Therefore, as a pragmatic approach, and in line with the phase 1 study, it was decided that a single infusion protocol should be adopted to simplify the participant journey and ensure adequate recruitment. This was agreed with the trial steering committee (TSC), sponsor and data monitoring committee (DMC).

**Figure 1 F1:**
[figure not shown]
Schematic of trial timeline.

## Methods

### Study oversight

The MATCH 0.1 trial is an investigator-led study, funded by the Medical Research Council (reference MR/M007588/1) and sponsored by ACCORD (Academic and Clinical Central Office for Research and Development for National Health Service (NHS) Lothian/University of Edinburgh). Trial oversight is also provided by a TSC and DMC, who are impartial around aspects of study design and logistics but provide independent advice and interval safety analyses. The study started initially in 2016 and is likely to continue until late 2022. All study-related documents were designed by the trial team with input from ACCORD, an independent statistician and the Scottish National Blood Transfusion Service (SNBTS) team. The trial will be conducted according to the ethical principles of the Declaration of Helsinki 2013 and has been approved by Scotland A Research Ethics Committee (reference 15/SS/0121), NHS Lothian Research and Development department and the Medicine and Health Care Regulatory Agency (MHRA-UK). Good Clinical Practice regulations will be followed and written informed consent will be obtained from all participants.

### Study setting

The MAcrophage Therapy for iver CirrHosis (MATCH) trial is recruiting in three hepatology centres in Scotland: Royal Infirmary of Edinburgh (Tertiary Transplant Centre/level 3 hepatology services), Ninewells Hospital, Dundee and Glasgow Royal Infirmary (both level 2 hepatology centres). There are plans to potentially extend recruitment to include additional sites.

### Patient and public involvement

There was no direct patient or public involvement groups involved in the study design. The overall study design was developed from previous experience of the investigators involved in the design and coordination of similar studies.

## Eligibility criteria (inclusions/exclusions)

### Inclusion criteria

Aged between 18 and 75 years (inclusive) at time of screeningAetiology: One or more of:Alcohol-related liver disease (no active alcohol misuse ≥6 calendar months prior to screening). Features of chronic liver disease with a compatible history of alcohol excess (>80 g/day), in the absence of other causes of chronic liver disease.PBC 2 out of: Cholestatic liver function tests (LFTs), Positive antimitochondrial antibody (titre >1:40). Compatible liver histology (if already receiving ursodeoxycholic acid must be established on current dose >3 months prior to enrolment).NAFLD Either: Histological evidence of hepatic steatosis in the absence of other liver diseases Or: Imaging compatible with NAFLD (eg, fatty infiltration of liver) and one or more risk factors (eg, elevated body mass index, type 2 diabetes mellitus, hypertriglyceridaemia, hypertension) and the absence of significant alcohol consumption (<20 g/day) and no evidence of other causes of chronic liver disease.Cryptogenic cirrhosis diagnosis of cirrhosis unattributable to any other cause.Haemochromatosis diagnosis made on basis of compatible biochemistry (transferrin saturation >60%, ferritin >400), genotype (homozygous C282Y or H63D compound heterozygote) or histology.Alpha-1 antitrypsin deficiency diagnosis based on compatible genetic, phenotypic or histological testing.Previous chronic hepatitis C (sustained viral response ie, undetectable HCV RNA 24 weeks after treatment).Diagnosis of cirrhosis—invasive or non-invasive criteria cirrhosis defined as any of:Biopsy-confirmed diagnosis of cirrhosis.Transient elastography (TE)—≥15 kPa.Clinical and radiological features which in the opinion of the investigator correlate with a diagnosis of cirrhosis.A MELD score (Pre-2016) of ≥10 and ≤17 at screening visit.

### Exclusion criteria

Refusal or inability to give written informed consent to participate in the study.

Other causes of chronic liver disease/cirrhosis not included in the listed aetiologiesPortal hypertensive haemorrhage; active episode of bleeding requiring hospitalisation in the last 3 months where varices have not been eradicated by endoscopic band ligation or transjugular intrahepatic portosystemic shunts (TIPSS).Ascites unless, in the opinion of the investigator, is minimal and well controlled with no increase to diuretic therapy in the last 3 months.Hepatic encephalopathy; current or requiring hospitalisation for treatment in the last 3 months.HCC—uncertain cases to be discussed at the local hepatobiliary multidisciplinary team meeting. Dysplastic or indeterminate nodules to be excluded; regenerative or other nodules to be included at discretion of investigator.Previous diagnosis of HCC.Previous organ transplant recipient.Listed for liver transplantation.Any situation that in the investigators opinion may interfere with optimal study participation such as alcohol or drug abuse, domicile too distant from study site, potential non-compliance or inability to cooperate.Presence of clinically relevant acute illness which may preclude on basis of safety.Presence or history of cancer with exception of adequately treated localised skin carcinoma, in situ cervical cancer or solid malignancy excised in total, with no recurrence (5-year interval).Pregnancy or breast feeding.

### Interventions

Participants who are randomised to the treatment arm will receive an infusion of the maximum achieved dose up to 1×10^9^ (day 0). The apheresis product will be collected under the terms of the Human Tissue (Quality and Safety for Human Application) Regulations 2007 No. 1523 enacting the requirements of the EU Tissues and cells Directive (2004/2023) and associated Commission Directives at the Apheresis Unit (Royal Infirmary of Edinburgh, Edinburgh, UK). CD14+ monocytes will be isolated, and the macrophage cell product will be manufactured as previously described,^25^ in compliance with GMP regulations under the terms of the SNBTS MIA (IMP) licence at the SNBTS Cell Therapy Facility (Scottish Centre for Regenerative Medicine, Edinburgh, UK).

Each patient will be monitored closely during the infusion to identify potential hypersensitivity reactions and 4 hours postinfusion bloods to monitor for any evidence of macrophage activation syndrom. A total of 28 participants will be randomised to standard medical care and 28 to receive the cell infusion, allowing for original estimate of 5 dropouts from each arm. Additional safety data will be collected for the first infusion only for the first three patients randomised to the treatment arm. If it has not been possible to achieve 1×10^9^ macrophages, then the participants will be infused with the quantity obtained, with minimum concentration being 1.25×10^8^ cells. This minimum cell concentration was derived from previous validation work and is stipulated as part of the product release criteria as designated by the MHRA.

### Outcomes

#### Primary outcome measure

##### Model of End-Stage Liver Disease

The MELD was originally devised to predict survival in patients with complications of portal hypertension undergoing elective placement of TIPSS. The algorithm is based on: creatinine, bilirubin and prothrombin ratio and has been demonstrated to be superior to the Child-Turcotte-Pugh score in predicting 3-month mortality among patients with end-stage liver disease.^26^ However, the MELD score has also been applied to predict survival in patients with cirrhosis with infections, variceal haemorrhage, and those with fulminant hepatic failure and alcoholic hepatitis.^27^

#### Secondary outcome measures

##### Transplant-free interval

The number of participants in each of the two treatment arms who are transplant free at 12 months will be expressed as proportions and a binomial test will be used for the comparison of proportions between the treatment arm and the control arm. The difference in proportions will be presented along with the 95% CI for the difference in the proportions.

The time to death or transplant will be presented using a Kaplan-Meier survival curve stratified by treatment and accompanied by a log-rank statistic comparing the two arms. Survival estimates with be presented by treatment arm at 3, 6, 9 and 12 months.

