##### Non-invasive markers of fibrosis

Changes in our secondary outcome measures over 90 days up to maximal 360 days as per schedule (table 1), these include: serum enhanced liver fibrosis (ELF) test (iQur, London, UK, serum Protein Fingerprint markers (Nordic Bioscience, Herlev, Denmark), hepatic TE (Echosens, Paris, France) and the UK End-Stage Liver Disease (UKELD) score.

**Table 1 T1:** Trial assessment schedule

	Visit 1a	Visit 1b	Treatment group				Control group					
			Visit 2a Within 7±4 days of Visit 1b	Visit 2b 7>10 days after apheresis (Day 0)	Visit 2c (Day 7)	Visit 2d (Day 14)	Visit 2 (day 7±4 days from visit 1b)	Visit 3 (Day 28*±4* days)	Visit 4 (Day 56*±4* days)	Visit 5 (Day 90*±7* days)	Visit 6 (Day 180*±7* days)	Visit 7 (Day 360*±7* days)
Informed consent	X											
Clinical assessment	X	X	X	X	X	X	X	X	X	X	X	X
Vital signs	X	X	X	X	X	X		X	X	X	X	X
Screening blood tests	X											
ECG	X											
Standard blood tests	X	X		X	X	X		X	X	X	X	X
Research bloods*			X		X	X	X	X	X	X	X	X
Mandatory microbiology	X		X									
Ferritin	X			X†	X	X						
Triglyceride	X			X†	X	X						
Pre-infusion blood tests				X								
MELD/UKELD	X	X		X	X	X		X	X	X	X	X
Pregnancy test	X‡	X‡		X‡	X§							X‡
Abdominal Ultrasound Scan (USS)	X¶										X¶	X¶
Fibroscan	X									X	X	X
ELF panel	X							X	X	X	X	X
Protein fingerprint	X¶							X¶		X¶		
CLDQ		X								X	X	X
31P MRS MRI**	X*									X		
Adverse events	X	X	X	X	X	X	X	X	X	X	X	X
Clinical events	X	X	X	X	X	X	X	X	X	X	X	X
Concomitant Medication	X	X	X	X	X	X	X	X	X	X	X	X

*If pass screen and before visit 2b.

†Obtain before discharge.

‡women of child bearing age only.

§If test not carried out at previous visit.

¶Fasted visit.

**Royal Infirmary of Edinburgh (RIE) patients only.

CLDQ, Chronic Liver Disease Quality of Life Questionnaire; ELF, enhanced liver fibrosis; MELD, Model for End-Stage Liver Disease; MRS, MR spectroscopy; UKELD, UK Model for End-Stage Liver Disease.

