### Sample size/power calculation

To detect a difference in the baseline to 90-day change in MELD score of 1 SD using a two-sided, two-sample test with a 5% level of significance, a sample size of 23 per group to detect the same level of difference with 90% power is required. All analyses will be carried out on an intention to treat basis, retaining participants in their randomised treatment groups irrespective of the treatment received. Adverse event (AE) data will be presented by treatment received.

The number of participants who do not adhere to the protocol is expected to be low. All protocol violations and ineligible participants will be recorded.

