### Data management

The following personal data will be collected as part of the research: name, date of birth and CHI numbers (Community Health Index; a unique is a 10-character numeric identifier, allocated to each patient on first registration with the NHS system in Scotland). Personal data will be stored in locked cabinets by the research team at the clinical research facilities at each site. Personal data will be stored for 30 years in keeping with the blood safety and quality regulations. The University of Edinburgh and NHS Lothian are joint data controllers along with any other entities involved in delivering the study that may be a data controller in accordance with applicable laws.

All investigators and study site staff involved with this study must comply with the requirements of the appropriate data protection legislation (including where applicable the general data protection regulation regarding the collection, storage, processing and disclosure of personal information. Access to personal information will be restricted to individuals from the research team treating the participants, representatives of the sponsor(s) and representatives of regulatory authorities.

Study data will be collected and managed using Research Electronic Data Capture (REDCap) electronic data capture tools hosted at The University of Edinburgh. REDCap^39^ is a secure, web-based application designed to support data capture for research studies, providing: an intuitive interface for validated data entry; audit trails for tracking data manipulation and export procedures; automated export procedures for seamless data downloads to common statistical packages; and procedures for importing data from external sources.

Published results will not contain any personal data that could allow identification of individual participants.

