### Statistical analysis plan

The baseline to 90-day change in MELD score will be compared in the two treatment arms using a two-sample t-test or non-parametric equivalent as appropriate. MELD scores calculated for each participant throughout the trial will be used to calculate an area under the curve (AUC) and this will be compared across the groups using a two-sample t-test or non-parametric equivalent as appropriate. In the event of varying durations in the trial follow-up, the average AUC per month will be used so that all participants have a comparable measurement.

Changes in secondary outcome measures (ELF score liver stiffness, CLDQ score, transplant-free survival, number of clinical events, UKELD score, blood parameters (bilirubin, albumin, ALT, INR)) over the 1-year study period will be presented graphically by dose. Similarly, these results will used to calculate an AUC for each participant and will be compared across the groups using a two-sample t-test or non-parametric equivalent as appropriate.

The only planned subgroup analysis is to present the primary outcome by disease aetiology (ALD, NAFLD, other). Primary data analysis will be conducted on participants who receive a single infusion versus control; the primary analysis will then be repeated to include those subjects who receive more than one infusion (three individuals). There are no plans for an interim analysis.

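### The only stated 12-month difference and 95% CI for transplant-free status rest on a crude proportion that cannot use partial follow-up; the Kaplan-Meier estimates already planned should supply them (minor)

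*Protocol article*

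**What the plan says.** All references are to the Protocol article.

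- **Transplant-free interval** fixes the 12-month analysis: "The number of participants in each of the two treatment arms who are transplant free at 12 months will be expressed as proportions". The section compares the arms on these figures by a binomial test and asks for the between-arm difference with its 95% CI. No denominator is given for participants whose 12-month status is unknown.
- The same section also plans Kaplan-Meier curves for time to death or transplant, a log-rank comparison of the arms, and survival estimates by arm at 3, 6, 9 and 12 months. It states no between-arm difference or CI for those estimates.
- **Interventions** sets 28 participants per arm, "allowing for original estimate of 5 dropouts from each arm".
- **Sample size/power calculation** says "All analyses will be carried out on an intention to treat basis", and explains this as keeping participants in their randomised groups whatever treatment they received.
- **Statistical analysis plan** adjusts the area-under-the-curve analyses for unequal follow-up: "In the event of varying durations in the trial follow-up, the average AUC per month will be used". The 12-month proportion has no counterpart to this.
- **Introduction** cites a one-year mortality of "4.4% in those with compensated disease".
- **Data management** lists the personal data collected: "name, date of birth and CHI numbers".

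**The concern.** A crude 12-month proportion needs 12-month status for everyone in its denominator. A participant last seen alive and untransplanted at six months must be counted as a success, counted as a failure, or left out. A Kaplan-Meier estimate uses those six months and makes none of these choices.

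The choice matters here because the dropouts allowed for outnumber the events to be expected. The trial is open-label, only one arm has apheresis and infusion, and the two arms have different visits, so unequal retention is plausible. Prolonged transplant-free survival is a named secondary objective. The only effect estimate with an interval planned for it at 12 months is the one that cannot handle censoring.

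**Working it through.** **Inputs.** 28 randomised and 5 dropouts allowed per arm (Interventions); 23 per group needed for the primary outcome (Sample size/power calculation); one-year mortality 4.4% (Introduction). The article gives no event rate for this trial, so 2% to 10% is taken as an assumed range. Transplants should add little early on, because patients already listed are excluded.

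**1. The plan's own figure.** A difference of 1 SD, two-sided 5%, 90% power: the exact two-sample t-test needs 22.02, so 23 per group. 23 + 5 = 28. The figure reproduces, and it shows that the 5 dropouts belong to the 90-day MELD calculation.

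**2. Events against dropouts, per arm.** 28 × 0.044 = 1.2 deaths; 28 × 0.02 = 0.56; 28 × 0.10 = 2.8. Allowed dropouts: 5, and 5/28 = 17.9%. Dropouts exceed expected events across the whole range.

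**3. Level within one arm, with 1 event and 5 of unknown status.**

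| Rule | Transplant free |
|---|---|
| Unknown = failure | 22/28 = 78.6% |
| Completers only | 22/23 = 95.7% |
| Unknown = transplant free | 27/28 = 96.4% |
| Kaplan-Meier | 1 − 1/23 = 95.7% (all 5 censored before the event) to 1 − 1/28 = 96.4% (all after) |

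**4. Difference between arms.** With the same data in both arms and one rule for both, the difference is 0 and p = 1 under all three rules. It moves when dropout is unequal and unknown status counts as failure. With equal 4.4% risk, the expected proportion is 0.956 × (1 − d/28) for d expected dropouts:

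- 2 v 5: 0.956 × 26/28 − 0.956 × 23/28 = 88.8% − 78.5% = 10.2 points
- 2 v 8: 0.956 × 26/28 − 0.956 × 20/28 = 88.8% − 68.3% = 20.5 points

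The true difference is zero in both cases.

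**5. False-positive rate.** Fisher's exact test, two-sided 5%, 28 per arm, 4.4% risk in both arms, dropout binomial and independent of events:

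| Expected dropouts | Unknown = failure | Completers only |
|---|---|---|
| 5 v 5 | about 2% | about 0.4% |
| 2 v 5 | about 9% | about 0.5% |
| 2 v 8 | about 34% | about 0.4% |

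The 2 v 5 and 2 v 8 splits are illustrations; the document does not give them.

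**6. Trials with no events.** With complete follow-up at 4.4%, one given arm has no event with probability 0.956^28 = 28%, and neither arm has one with probability 0.956^56 = 8%. Simulating 5 v 5 dropouts spread evenly over the year, neither arm shows an event in about 10% of trials. Greenwood's variance is zero in an arm without events, so a standard Kaplan-Meier interval collapses there.

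**The case against.** The case against is substantial, and much of it stands.

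- **The harmful rule is not in the text.** The article does not say that dropouts count as failures, and its intention-to-treat sentence concerns treatment received, not unknown status. The rule may be set in the full protocol or the SAP, which are not shown, so its absence is no finding. What remains is the stated estimator: whatever rule is chosen, a crude proportion cannot use partial follow-up.
- **A censoring-aware comparison is already planned.** The log-rank test compares the arms on death or transplant. This stands. A p-value, however, is not a 12-month difference with an interval, and only the crude proportion is given one.
- **The 5 dropouts are a 90-day allowance.** A participant who stops attending need not have unknown death or transplant status. This stands too; the figure only indicates the scale.
- **The 4.4% is background mortality** for compensated disease, not a design assumption for patients with MELD 10 to 17. The assumed range of 2% to 10% leads to the same conclusion.

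A reader might infer that missing status, not outcome, decides the result. The documents do not support that. At the plan's own allowance of 5 v 5, even counting unknown as failure gives a false-positive rate of about 2%. Inflation needs both that unstated rule and unequal dropout. A reader might also infer from "Visit 7 (Day 360*±7* days" that completers seen before Day 360 lack 12-month status. That is a routine visit window around the nominal 12-month visit and is not a defect.

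**Conclusion.** The point holds in a limited form, and its severity is minor. The plan attaches its only 12-month difference and 95% CI for transplant-free status to an estimator that cannot use partial follow-up, although a better one is planned in the same section. If unknown status counts as failure and dropout differs by arm, the bias equals the gap in retention scaled by the event-free proportion: about 10 points at 2 v 5. With equal dropout the expected difference is unaffected. With completers only, the false-positive rate stays below 1% and the bias is under 1 point at 4.4% risk.

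This rests on the cited 4.4% standing in for the trial's own risk, on dropout unrelated to outcome, and on dropouts having unknown status. The last may be untrue if records are checked.

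**What to change.** In Transplant-free interval, take the 12-month between-arm difference and 95% CI from the Kaplan-Meier estimates of freedom from death or transplant, read at the nominal 12-month visit. Keep the log-rank test as the comparison of the arms. The crude counts can stay as description, with their denominator stated.

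Name an interval method that does not collapse when an arm has no events. One option is a Wilson-type interval for each arm, based on an effective sample size and combined across arms by Newcombe's approach.

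Where consent permits, confirm death and transplant status for participants who stop attending, using the CHI numbers already held. This attacks the problem at its source.

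The cost is one or two changed sentences, a check of at most 56 records (28 + 28), and possibly a check of consent or ethics wording. The downside is an interval that is only approximate when events are few.
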